### Measures

#### Outcomes and Instruments

For the purposes of this study, outcomes were divided into clinical, psychosocial, and biological domains to make the study as comprehensive as possible in understanding the complex processes of change that may occur in psychotherapies (Table 1). The clinical domain refers to the more traditional measures of symptoms used to mediate the effectiveness of psychotherapy (13, 14). The psychosocial domain relates to the most current tendency of understanding the impact of an intervention on a patient’s functionality, general well-being, and quality of life (10). The biological domain will evaluate the impact of psychotherapy on BDNF (23, 32).

**Table 1 T1:** Assessments according to time of psychotherapy.

Outcomes/confusion factors	Baseline	6 months	12 months
1. Primary outcomes			
1.1 Clinical domain			
Depression symptoms (BDI)	X	X	X
Anxiety symptoms (BAI)	X	X	X
Psychiatric symptoms (SCL-90-R)	X	X	X
1.2 Biological domain			
Serum BDNF	X	X	
1.3 Psychosocial domain			
Quality of life (WHOQOL-BREF)	X	X	X
Resilience (CDRISC)	X	X	X
Social support (MOS)	X	X	X
Quality of life-adjusted years (SF-6D)	X	X	X
2. Confusion/mediator factors			
2.1 Clinical domain			
Diagnosis (review of medical records)	X		
Psychodynamic Diagnosis (OPD-II)	X	X	
			
Comorbidities	X		
Pharmacological treatment	X	X	X
Personality traits (PID-V)	X		X
Number of sessions		X	X
Type of psychotherapy	X		
2.2 Psychosocial domain			
Psychosocial stressors (LEQ)	X	X	X
Therapeutic alliance (CALPAS)	X	X	X
Motivational status (URICA)	X	X	X
Defense mechanism style (DSQ-40)	X	X	X
			
2.3 Others			
Religiosity (DUREL/WHOQOL-SRPB BREF)	X	X	X

BDI, Beck Depression Inventory; BAI, Beck Anxiety Inventory; SCL-90-R, Symptom Checklist-90—Revised; BDNF, brain-derived neurotrophic factor; WHOQOL-BREF, World Health Organization Quality of Life BREF; CD-RISC-25, Connor–Davidson-25 Scale of Resilience; MOS, the Medical Outcomes Study; SF-6D, Short-Form Six-Dimension; OPD-II, Operationalized Psychodynamic Diagnosis; PID-V, the Personality Inventory for DSM-5; LEQ, the Life Events Questionnaire; CALPAS, California Psychotherapy Alliance Scale; URICA, The University of Rhode Island Change Assessment; DSQ-40, The Defense Style Questionnaire; DUREL, Duke University Religion Index; WHOQOL-SRPB-BREF, World Health Organization Quality of Life BREF—Spirituality.

##### Domain of Clinical Variables

###### Psychiatry Symptomatology—General Symptomatology

The Symptom Checklist-90-Revised (SCL-90-R) is a self-administered scale consisting of 90 items distributed over nine dimensions: somatization, depression, interpersonal, obsessive–compulsive sensitivity, anxiety, hostility, phobic anxiety, paranoid ideation, and psychoticism. The scales of answers range from 0 (not at all) to 4 (an extreme degree of injury). Over the 6 months after discharge from the clinical follow-up, only paranoid ideation and the psychosis domains are considered. This situation results in a total of 16 items. The next follow-ups are conducted face to face, which allows for the application of the entire checklist (33).

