## Aims

Our primary aim is to evaluate the outcomes associated with different forms of individual psychotherapy [psychodynamic psychotherapy (PDT), interpersonal psychotherapy (IPT), and CBT] in a public outpatient clinic for mental disorders. Our primary outcomes are divided into three domains of variables: clinical (general psychiatric symptoms), biological (serum BDNF levels), and psychosocial (resilience, quality of life, social support, and quality of life-adjusted years of life).

Our secondary aim is to evaluate potential confounders/mediators/moderators for the main outcomes: personality traits, type of psychotherapy, number of sessions, the therapist’s duration of training, concomitant use of pharmacological treatment, history of previous psychotherapeutic treatment, medical and psychiatric comorbidities, psychiatric diagnosis, therapeutic alliance, and defense mechanisms.

Our main hypothesis is that all three modalities of therapy will produce reduction of symptoms in the clinical domain and improvement in the psychosocial domain. All psychotherapies will increase BDNF at 6 months of follow-up. As secondary hypotheses, the mechanisms of improvement will be mediated by the therapeutic alliance, motivational status, and defense mechanisms (for PDT). The confounders of this therapeutic improvement will be number of sessions, comorbidities, and medication use. The moderating factors will be gender, age, personality traits, religiosity, and defense mechanisms (for CBT).

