#### Sample Size Estimation

Our sample size calculation relied on the study of Schaf (51) using BDNF serum levels before and after psychotherapy as outcomes. We arrived at a number of 42 subjects for each psychotherapy and control group, considering a significance level of 5% and a power of 80% difference to be detected 0.22 with a standard deviation of 0.43 and losses of 20–30%. We estimated a total sample size of 126 patients and 42 blood donor healthy controls for biological variable (as comparative of BDNF samples). The inclusion criteria will include having started psychotherapy within 1 month, an age above 18 years, and a BDI score greater than 15. The exclusion criteria will include psychotic disorders, current use of psychoactive substances, cognitive deficits, and dementias.

The study will include a subsample of healthy controls for control of blood samples that were recruited from the HCPA blood bank. The exclusion criteria for the control group included conditions (current or past) that precluded participation in the study (e.g., psychiatric disorders and/or psychiatric treatments), immune disorders, use of immunosuppressants, anti-inflammatory drugs used for fewer than 3 weeks, smoking, abuse and/or drug addiction, and infectious diseases for fewer than 3 weeks.

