### Procedure

The study will be disseminated through the presentation of its protocol in meetings with the outpatient services of the HCPA that refer patients to the psychiatry service, such as the internal medicine, pain, and bariatric surgery outpatient clinic.

The researchers will not participate in the indication of treatment of patients or in their assistance. Patients will be sought weekly in the HCPA outpatient medical records and through contact with resident physicians screening new patients. Those who fall into the eligibility criteria will be contacted by phone by the research assistant and invited to participate. It will be explained that refusal to participate will not entail any loss to the treatment. If they agree to participate, they will be asked to attend the HCPA Clinical Research Center (CPC-HCPA), where they will receive the informed consent form, sociodemographic interview, OPD interview, BDNF blood collection, and protocol with self-administered questionnaires. The consent form and OPD will be applied by the researchers. Patients will be contacted by telephone for the follow-up of 6 and 12 months (Figure 1).

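### The 16-item rule for the SCL-90-R contradicts Table 1 and, if applied at 6 months, leaves no general-symptom score comparable with baseline

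*Protocol article*

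**What the plan says.** The Aims section of the protocol article gives the primary outcomes as "clinical (general psychiatric symptoms), biological (serum BDNF levels), and psychosocial (resilience, quality of life, social support, and quality of life-adjusted years of life". Table 1, under the clinical domain of primary outcomes, has the row "Psychiatric symptoms (SCL-90-R") marked at baseline, 6 months and 12 months. No footnote or entry points to a reduced form. The BDI and BAI are marked at the same three times.

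The section Psychiatry Symptomatology—General Symptomatology describes the SCL-90-R: it "is a self-administered scale consisting of 90 items distributed over nine dimensions". It then adds a restriction, "Over the 6 months after discharge from the clinical follow-up, only paranoid ideation and the psychosis domains are considered", and gives the resulting length as 16 items. It continues: "The next follow-ups are conducted face to face, which allows for the application of the entire checklist".

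The Design section sets three assessments: baseline, then 6 and 12 months, both counted from study entry. Table 1 also marks serum BDNF at baseline and 6 months, and the Blood Collection text says that the samples are taken by venipuncture. The Procedure section says: "Patients will be contacted by telephone for the follow-up of 6 and 12 months".

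**The concern.** The instrument description and Table 1 cannot both be followed. One has the complete SCL-90-R at each visit. The other has a period in which only two of its nine dimensions count. The rule is also tied to a discharge, whereas the study follows outpatients from entry and the article sets out no discharge step. A site reading the article could not tell which form to give at which visit.

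What is at stake is a primary outcome. The main hypothesis is a reduction of symptoms, and the Statistical Analysis section plans GEE for repeated measurements. If one of the three assessments holds only paranoid ideation and psychosis items, a general-symptom score at that visit is not the same measure as at the other two. Six months is also the only follow-up with BDNF, so the full SCL-90-R would be absent at the one follow-up where its change could be set beside change in BDNF. Items that are not collected cannot be recovered later.

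**Working it through.** **Inputs.** From the SCL-90-R description: 90 items, nine dimensions, and "The scales of answers range from 0 (not at all) to 4 (an extreme degree of injury"), so at most 4 points per item; under the restriction, two dimensions and 16 items. The article does not list items per dimension, so the 16 is taken as stated. From the Design section: two follow-ups, at 6 and 12 months after entry.

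**Step 1: which visit the rule can refer to.**

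| Place | What it implies for the SCL-90-R |
|---|---|
| Table 1 | Baseline, 6 and 12 months, no reduced form |
| Instrument description, first part | 90 items, self-administered |
| Instrument description, restriction | 16 items over a 6-month period counted from discharge |
| Instrument description, last part | Full checklist at the face-to-face follow-ups that come next |
| Design | Visits counted from entry, no discharge defined |

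A short form followed by a later full form, in a schedule with two follow-ups, fits the 6-month visit best. It does not fit perfectly: the text speaks of later follow-ups in the plural, and only one would remain. On every reading the restriction disagrees with Table 1 and uses a time origin that the Design section does not have.

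**Step 2: what is lost if the rule is applied at 6 months.**

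- Items dropped: 90 − 16 = 74, and 74/90 = 82%.
- Items kept: 16/90 = 17.8%.
- Dimensions dropped: 9 − 2 = 7.
- Maximum raw total, full form: 90 × 4 = 360.
- Maximum raw total, reduced form: 16 × 4 = 64.

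Dividing by the number of items would put both forms on a 0 to 4 scale, but would not make them comparable. The 6-month mean would describe two dimensions and the baseline mean would describe nine.

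**Step 3: what is not lost.** The two retained subscales can be followed over all three visits. The change from baseline to 12 months is available for all nine dimensions if the full form is given at 12 months. The BDI and BAI are unaffected. So is the sample size: 42 per psychotherapy group (3 × 42 = 126) was derived from BDNF, not from the SCL-90-R.

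**Step 4: whether the implied reason for a short form holds.** The description says that face-to-face contact is what permits the entire checklist. Blood is drawn at 6 months, so the patient attends in person then, and the scale is self-administered in any case. By the article's own reasoning there is no obstacle to the full form at that visit.

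**The case against.** The strongest objection is that the article never says in so many words that the 6-month visit uses 16 items. The rule runs from a discharge that this study lacks, the plural for later follow-ups does not suit a schedule with only one visit left, and the blood draw makes the 6-month visit an in-person one, where the full checklist would be allowed. The sentence may be misplaced or poorly adapted text, with Table 1 governing. This stands: the link to 6 months is an inference. It does not remove the contradiction, because the sentence is in the current text and nothing says that Table 1 prevails.

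Several stronger readings are tempting and are not supported:

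- **That 6-month response in depression and anxiety goes unmeasured.** The BDI and BAI are themselves listed as primary clinical outcomes at that visit.
- **That the retained items would sit near the floor.** A reader might infer this because "The exclusion criteria will include psychotic disorders", but the article gives no score distribution. The sample can include patients with personality disorder, so paranoid ideation cannot be called irrelevant.
- **That the Procedure section contradicts face-to-face follow-up.** The same section has patients telephoned at entry and then asked to attend the research centre, so the later call may also be only an invitation. The text leaves this open.
- **That a GEE model will certainly mix the two forms.** This holds only if a total or global score is analysed. The article names none, and that choice may properly sit in the full protocol or analysis plan.

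**Conclusion.** The concern holds as an internal contradiction about a primary outcome. The SCL-90-R description restricts the scale to 16 of 90 items for a 6-month period, Table 1 shows no restriction, and the Design section has no discharge from which to count.

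The size of the consequence is conditional. Assuming that the rule is applied at the 6-month visit and that a general-symptom score is wanted there, 74 items (82%) and 7 of 9 dimensions are missing, and the baseline-to-6-month change in general symptoms on this scale cannot be estimated. If Table 1 governs, nothing is lost and only the wording is wrong. The documents do not settle which applies. They do not support a claim that all symptom information at 6 months is lost. The point should still be settled before 6-month data are collected, since the loss would be permanent and preventing it is cheap.

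**What to change.** Delete the 16-item rule, with its reference to discharge, from the SCL-90-R description so that it agrees with Table 1 and the Design section. State that the full self-administered SCL-90-R is given at baseline, 6 and 12 months, at 6 months alongside the BDNF blood draw. In the Procedure section, say whether the telephone contact at 6 and 12 months is an invitation to attend or the mode of assessment, so that it can be read together with the face-to-face statement.

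The cost is a wording change and, compared with the reduced form, 74 more self-report items per patient at a visit that already takes place. The planned number of patients does not change.

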###### Symptoms of Anxiety and Depression: Beck Depression Inventory and Beck Anxiety Inventory (BAI)

These self-report rating inventories, developed by Beck, aim to measure symptoms of depression and suicidal ideation [Beck Depression Inventory (BDI)] and anxiety [Beck Anxiety Inventory (BAI)] (34).

##### Domain of Biological Variables

###### Serum Levels of BDNF

*Blood Collection* Serum samples will be obtained by venipuncture, and the blood will be immediately centrifuged at 3,000 × *g* for 5 min. The samples will be stored at −80°C until biochemical analysis.The levels of neurotrophins (BDNF) will be measured using a sandwich ELISA kit (enzyme-linked immunosorbent assay; Elabscience^®^, Houston, TX, USA), according to the manufacturer’s instructions, with techniques standardized by our group. The total quantity of proteins was measured according to the Lowry method.
*Storage and Analysis of Blood Samples* The laboratory tests will be conducted at the Molecular Psychiatry Laboratory. The samples were stored in an appropriate laboratory managed by Gupo de Pesquisa e Pós-Graduação do Hospital de Clínicas de Porto Alegre (GPPG–HCPA).

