#### Statistical Analysis

Shapiro–Wilk test will be used to determine normality. For parametric distributions, dependent or independent *t* tests will be performed. To determine differences between categorical variables, the chi-squared test will be used. For nonparametric distributions, we will use the Wilcoxon test and Mann–Whitney *U* test to compare nonrelated and related means, respectively. A generalized estimating equations (GEE) model will be used to investigate multivariate repeated measurements. The Hayes method will be used to analyze the mediators (52), and the multivariate regression will be used to analyze the confounders. *Post hoc* analyses will be performed using the Bonferroni test.

The data will be expressed as mean ± standard deviation (SD), and a *p* value less than or equal to 0.05 will be considered to be statistically significant (two-tailed). The statistical analyses will be performed using the SPSS version 20.0 software package (IBM^®^, New York, USA).

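### The article calls the BDNF samples serum but has the blood centrifuged immediately, with no clotting interval, so the primary biological outcome may not be the analyte named

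*Protocol article*

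**What the plan says.** The Blood Collection text under Serum Levels of BDNF reads: "Serum samples will be obtained by venipuncture, and the blood will be immediately centrifuged at 3,000" × g, for 5 minutes. It continues: "The samples will be stored at −80°C until biochemical analysis". No tube type, clot activator or clotting interval is given. The ELISA is to be run "according to the manufacturer’s instructions, with techniques standardized by our group". The next paragraph, on storage, slips into the past tense, so some samples may already exist.

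The outcome matters to the design in three places:

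- Aims lists serum BDNF as the biological primary outcome, and Table 1 schedules it at baseline and 6 months.
- The main hypothesis in Aims includes "All psychotherapies will increase BDNF at 6 months of follow-up".
- Sample Size Estimation relies on an earlier study "using BDNF serum levels before and after psychotherapy as outcomes", and adds 42 healthy blood donors as the BDNF comparison group.

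**The concern.** The sample type and the handling step do not fit together. Serum exists only once blood has clotted, and blood spun straight after the draw has had no time to clot. A laboratory that followed the sentence as written would obtain plasma or incompletely clotted material, depending on the tube.

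This is more than a detail that a condensed article leaves out. The text fixes the time from draw to spin, the force and the duration, and the time it fixes conflicts with the name of the analyte.

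What is at stake is whether the measurement is the one named. The difference of 0.22 and SD of 0.43 come from before-after serum levels in another study. If the samples here are a different material, those inputs may not carry over. The patient and blood-donor values are also comparable only if both were prepared in the same way.

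**Working it through.** **1. The text side by side**

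| Item | What the article states | Where |
|---|---|---|
| Analyte | Serum BDNF | Abstract; Aims; Table 1; Serum Levels of BDNF |
| Time from draw to spin | Immediate | Serum Levels of BDNF |
| Clotting interval, tube type | Not stated | – |
| Kit instructions and group standardisation | Attached to the ELISA measurement | Serum Levels of BDNF |
| Same handling at both visits and in controls | Neither stated nor denied | Serum Levels of BDNF; Sample Size Estimation; Procedure |

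The first two rows conflict when read literally. The fourth does not resolve the conflict, because that clause concerns how the assay is run and not how the blood is prepared.

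**2. The plan's own sample size**

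Inputs from Sample Size Estimation: "considering a significance level of 5% and a power of 80% difference to be detected 0.22", SD 0.43, losses of 20–30%. Statistical Analysis specifies two-tailed tests. I assume that 0.43 is the SD of the before-after change.

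- Normal approximation: n = (0.43 × (1.960 + 0.842) / 0.22)² ≈ 30.
- Noncentral t: n = 32 (power 80.1%).
- After losses: 30/0.75 = 40 and 30/0.70 ≈ 43; 32/0.80 = 40 and 32/0.75 ≈ 43.

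These all lie within 2 of the stated 42, so a paired comparison of serum BDNF reproduces the plan. A two-sample comparison does not: it needs 60 per group before losses. The study is therefore sized on the change in this one analyte.

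**3. What a uniform immediate spin would do to the change**

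- If it shifted every level by a constant c, the change would be (after − c) − (before − c) = after − before, with no effect.
- If it captured a constant fraction k of every level, the difference would be 0.22k and the SD 0.43k. The ratio stays at 0.22/0.43 = 0.51, and power is unchanged apart from any fixed assay noise.

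Uniform handling of either kind changes what is measured and how it compares with other serum data. It does not by itself reduce power.

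**4. Illustration only: if handling added variance**

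The documents give no figure for this, so the range is assumed. SD = 0.43 × √(1 + f); two-sided paired t test, 32 completers.

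| Assumed extra variance f | SD | Power |
|---|---|---|
| 0 | 0.430 | 80% |
| 10% | 0.451 | 76% |
| 25% | 0.481 | 71% |
| 50% | 0.527 | 63% |
| 100% | 0.608 | 51% |

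The table shows how sensitive the design would be. It does not estimate an effect of the blood-handling sentence.

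**The case against.** The strongest reply is that the sentence may only be loosely worded. It calls the material serum, which implies clotted blood, and the adverb may mean without delay once serum can be separated. Tube type and clotting time commonly sit in a laboratory procedure, which an article need not reproduce. This stands in part: the text does not exclude a clotting step, so it cannot be said that none takes place. It does not remove the point. A laboratory procedure that included clotting would contradict the article's sentence, and the sentence would still need correcting.

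A reader might also infer that BDNF will vary with handling, or that differences between visits, or between patients and donors, will look like a BDNF effect. The documents do not support this. An immediate spin is a single rule for all samples, and nothing shows that handling differs by visit, group or site.

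Nor do they support a stated loss of power. The variance inflations above are assumed. The SD of 0.43 was presumably observed in real samples and so already contains that study's handling noise. Shrinking the mean change to 80% or 60% while holding the SD fixed would give power of 61% or 39%, but under proportional capture the SD shrinks too.

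Finally, the documents say nothing about how clotting affects BDNF. The point made here needs only the definition of serum.

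**Conclusion.** The concern holds in a limited form. As written, the handling step does not produce the sample type that the article names as its primary biological outcome and uses to size the study. The two statements must be reconciled.

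The severity is moderate. This rests on a literal reading of the blood-collection sentence and on the definition of serum. The size of any effect on BDNF results cannot be derived from the documents, no loss of power is shown, and 42 per group stands. It would go too far to conclude that no clotting takes place, that the samples are certainly not serum, or that the BDNF comparison is biased.

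**What to change.** Replace the immediate spin with centrifugation after a fixed clotting period in a serum tube, with the period taken from the tube or kit instructions and the tube type named. State that the same interval applies at baseline, at 6 months and in the blood-bank controls. Record the draw and spin times for every sample.

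If samples have already been taken, establish how they were handled. If any were spun without clotting, flag them and run a sensitivity analysis with and without them.

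The cost is a changed line in the procedure, two clock times and a short standing time per sample. No extra blood draw is needed and the sample size is unaffected. The one real downside is that samples already taken cannot be corrected, only flagged.
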